### Endpoints

The primary endpoint is the 3-year DFS, which is measured from the time of randomization until locoregional failure, metastasis, secondary cancer, or all-cause mortality. The data of patients who have not experienced any events by the time of the analysis will be censored at the last follow-up date. The Kaplan-Meier method will be used to calculate the survival rates. The secondary endpoints are the pathological complete response (pCR) rate; proportions of pathologic tumor regression grade (TRG) (Dworak [12], Mandard [13], AJCC TRG system [14]; R0 resection (microscopically clear resection) rate, 60-day postoperative surgical morbidity and mortality; treatment-related toxicity using the Common Terminology Criteria for Adverse Events version 5.0 (CTCAE v5.0); compliance with the study protocol defined as the completion of preoperative treatment, surgery, and adjuvant treatment; TRG based on magnetic resonance imaging (MRI) [15]); quality of TME [16]; 5-year DFS; 3/5-year overall survival (OS); loco-regional recurrence; distant metastasis; 3-year peripheral neuropathy grade (CTCAE v5.0); questionnaires of quality of life (QoL) using the Korean version of the European Organization for the Research and Treatment of Cancer Quality of Life Questionnaire Core 30 (EORTC QLQ-C30) version 3.0 [17]; QLQ-CR29 [18]; Low Anterior Resection Syndrome (LARS) score [19]; 5-item version of the International Index of Erectile Function (IIEF-5) [20]; retrograde ejaculation from inclusion to 2 years after surgery; and cost-effectiveness (direct cost, indirect cost, and quality-adjusted life-year).

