### Follow-up

Each participant will undergo regular follow-up until 5 years following surgery for history and morbidity/toxicity assessment, physical examination, measurement of carcinoembryonic antigen (CEA), and assessment of questionnaires of QoL. Toxicity will be evaluated and recorded according to CTCAE v5.0. Furthermore, CEA will be measured at 3 months following surgery and every 6 months thereafter. Abdominopelvic and chest CT scans will be performed every 6 months during the first 2 years and then annually during the following 3 years. QoL assessment using EORTC questionnaires QLQ-C30 and QLQ-CR29, LARS score for all patients, and IIEF-5 for male patients will be performed at 3, 6, 12, and 24 months.

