### Statistical analysis

The primary endpoint will be analyzed according to the intention-to-treat principle in patients who are randomized and receive preoperative treatments. Secondary analyses will be conducted using the per-protocol principle, considering only patients with sufficient compliance with the protocol. The Kaplan–Meier curve will be used to analyze the survival outcomes and the log-rank test for the prognostic factors. The chi-squared test will be employed to compare categorical data between the two groups and Student’s *t*-test for continuous variables. The effect of covariates on the endpoints will be evaluated using the Cox proportional-hazards model. QoL, assessed using questionnaires, will be expressed as mean, standard deviation, median, minimum, and maximum values. A mixed model for repeated-measure analysis with the assumption of an unconstructed covariance structure will be applied for QoL comparison. Least-square mean estimates will be calculated for *post hoc* analyses to compare the two treatment groups at each time point and evaluate any changes from the baseline scores. All tests will be two-sided, and *P*-value < 0.05 will be considered to indicate statistically significant differences. This trial has no plan for interim analysis. Missing data for the primary endpoint will be censored at either the last assessment date or the trial deadline, whichever is earlier. Because the primary endpoint is presented as recurrence or not, there are no outlier data. If there are missing values for the secondary endpoints, the last observation carried forward method will be employed to impute for the missing data with the most recently available data, and the Grubb and Cochran tests will be adopted to determine outliers if suspected.

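### LOCF is prescribed for every missing secondary-endpoint value; used ahead of the planned mixed model, it would bias QoL and functional scores that change after the last observed visit

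*Protocol article*

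**What the plan says.** All of the analysis text is in the protocol article, Statistical analysis.

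- **Imputation rule.** Its scope is "If there are missing values for the secondary endpoints" and its method is that "the last observation carried forward method will be employed to impute for the missing data with the most recently available data". No endpoint is exempted.
- **QoL model.** "A mixed model for repeated-measure analysis with the assumption of an unconstructed covariance structure will be applied for QoL comparison". The covariance is read here as unstructured. Least-square means are then used "to compare the two treatment groups at each time point and evaluate any changes from the baseline scores".
- **Primary endpoint.** This has its own rule: "Missing data for the primary endpoint will be censored at either the last assessment date or the trial deadline, whichever is earlier".

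Follow-up schedules the EORTC questionnaires, the LARS score and the male questionnaire together: "IIEF-5 for male patients will be performed at 3, 6, 12, and 24 months". Endpoints lists all of these as secondary, alongside "5-year DFS; 3/5-year overall survival (OS); loco-regional recurrence; distant metastasis" and once-measured outcomes such as pCR, tumor regression grade and R0 resection.

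The section does not say whether the mixed model is fitted to observed or to LOCF-filled scores. It names no sensitivity analysis for missing QoL data.

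**The concern.** A likelihood-based mixed model with unstructured covariance uses each patient's observed visits and is valid under missing-at-random without imputation. If LOCF completes every series beforehand, no missing value is left for the model to handle, and a score frozen at an early visit counts the same as a measured one.

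Freezing is a poor assumption for these outcomes. The four visits span adjuvant chemotherapy of about 4 months and the period after it. Carrying a 3-month score to 24 months assumes no later change. Carrying the baseline score into a missed 3-month visit assumes no deterioration. The direction of the error therefore depends on when data go missing.

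The planned contrasts are exactly the affected quantities: arm differences at each visit and changes from baseline. The article's abstract anticipates a potential QoL advantage for the experimental arm, and its Discussion says new treatments should improve QoL as well as oncological outcomes. These scores would have to support that.

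**Working it through.** **The plan's own figures.** None concerns QoL missingness. The event count reproduces: HR = ln 0.80 / ln 0.70 = 0.626, and 4 × (1.645 + 0.842)² / (ln 0.626)² = 112.7, rounded up to 113. No input to it involves the secondary endpoints, so this point cannot alter it.

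**Step 1: a hand calculation. All inputs are assumptions.**
- Both arms have the same true mean change from baseline: −12 at 3 months, −8 at 6 months, 0 at 24 months.
- A fraction d of an arm drops out before 12 months, half last seen at 3 months and half at 6 months.
- LOCF mean change at 24 months = d × (0.5 × (−12) + 0.5 × (−8)) = −10d.

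| d | LOCF mean change at 24 months (true value 0) |
|---|---|
| 10% | −1.0 |
| 20% | −2.0 |
| 25% | −2.5 |

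The false arm difference is 10 × the difference in d. It is 1.0 point for 20% against 10%, 1.5 points for 25% against 10%, and 0 for equal dropout. Each arm's own change from baseline is wrong in all of these cases, including equal dropout.

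**Step 2: simulation.** There were 1,500 trials per scenario with 182 patients per arm (from Sample size calculation) and no true arm difference. Assumed inputs:
- means of 70, 55, 60, 68 and 72 at baseline, 3, 6, 12 and 24 months
- SD 20
- correlation 0.4 or 0.6, raised to the square root of the visit lag
- monotone dropout after 3 months that depends on the previous observed score

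Results at 24 months, shown as correlation 0.4 / 0.6:

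| Missing, by arm | LOCF arm means (true 72) | LOCF difference | LOCF rejection | Observed-data difference | Observed-data rejection |
|---|---|---|---|---|---|
| 10%, 10% | 70.3–70.5 | −0.07 / 0.03 | 4.1% / 5.3% | −0.09 / 0.01 | 4.1% / 5.5% |
| 20%, 20% | 68.6–69.0 | −0.04 / −0.01 | 4.9% / 5.1% | −0.02 / 0.00 | 4.9% / 4.9% |
| 30%, 30% | 66.8–67.4 | 0.08 / 0.02 | 4.9% / 4.5% | 0.07 / 0.01 | 4.7% / 5.6% |
| 10%, 20% | 70.3, 68.6 / 70.5, 69.0 | 1.68 / 1.56 | 10.5% / 10.7% | 0.00 / 0.00 | 4.8% / 5.5% |
| 10%, 30% | 70.3, 66.9 / 70.5, 67.4 | 3.44 / 3.08 | 34.7% / 28.0% | 0.05 / −0.01 | 5.3% / 5.1% |

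LOCF shifts arm means by −1.5 (70.5 − 72) to −5.2 (66.8 − 72) points. The model on observed data recovers 72.0 throughout. The arm comparison fails only in the rows with unequal missingness.

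**Step 3: standard errors.** The LOCF standard error is below that of the observed-data model in every scenario, by 0.5% (2.19 against 2.20) to 6.5% (2.32 against 2.48).

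The simulated curve has a deeper trough than Step 1 (72 − 55 = 17 points, against 12) and did not include 25% against 10%. It supports the direction and the conditions, but does not confirm the 1.5-point figure.

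**The case against.** **The two rules do not contradict each other.** A reader might infer that they cannot both be followed. They can, because a mixed model can be fitted to LOCF-filled data. This stands: the defect is a poor and unreconciled choice.

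**The treatment comparison need not be biased.** This also stands. With equal dropout and equal trajectories the arm difference stays near 0 and rejection near 5%. The only attrition figure in the article is 5%, given for the DFS sample size. A split around it of 7.5% against 2.5% gives 10 × 0.05 = 0.5 points on the Step 1 curve. With an assumed SD of 20, the standard error of a difference is 20 × √(2/182) = 2.1, so even 1.5 points is less than one standard error. Unequal missingness is plausible with such different preoperative regimens, but the documents do not quantify it.

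**The time-to-event and pathology endpoints suffer little.** A reader might infer that LOCF would be used for overall survival or pCR and give wrong results. The text does not support that. Statistical analysis assigns survival outcomes generally to Kaplan–Meier curves, which handle incomplete follow-up by censoring, and a once-measured outcome has no earlier value to carry. What remains is loose wording: the explicit censoring rule names only the primary endpoint, and the LOCF sentence excludes nothing.

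**Carrying scores past death or relapse is not stated.** Nothing says that values after death count as missing, or that questionnaires stop at relapse.

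**The 3-year neuropathy grade** falls within the rule as worded, but the mixed model is not planned for it and no calculation here covers it.

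An unseen SAP does not answer the main point, because the LOCF rule is stated text rather than an omitted detail.

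**Conclusion.** The concern holds for the repeated QoL, LARS and IIEF-5 scores. Followed as written, the LOCF rule removes the planned model's validity under missing-at-random. It biases arm means and changes from baseline whenever scores change after the last observed visit. Bias in the arm comparison additionally needs unequal amount or timing of missingness, or unequal trajectories.

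The size cannot be fixed from the documents. On the assumed recovery curve of Step 1, it is a false 1.0–1.5 points at 24 months for 10% against 20–25% dropout, and nothing for equal dropout with equal trajectories. Bias is the main harm. It would be too strong to call the standard errors seriously understated, since the gap in simulation was 0.5–6.5%.

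The advantage of the observed-data model itself rests on missing-at-random. If missingness depends on unobserved scores it can also be biased, which is why a sensitivity analysis is needed. The point should be fixed, but it touches secondary endpoints only and leaves the primary DFS analysis untouched.

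**What to change.** Amend the missing-data sentence in Statistical analysis, and the matching SAP text if there is one, as follows:

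1. Delete LOCF for the repeated QoL and functional scores (EORTC questionnaires, LARS, IIEF-5). State that the planned mixed model is fitted to observed scores without imputation.
2. Add a missing-not-at-random sensitivity analysis, for example a delta-adjusted one, with the range of deltas set before arms are compared.
3. State that LOCF does not apply to the time-to-event secondary endpoints, which are censored as for the primary endpoint, or to once-measured pathology outcomes.

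The cost is a wording change and slightly more analysis work. The 113 events, the 364 patients and the primary analysis are unchanged. No interim analysis is planned, so the change can be made before any comparison by arm.

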### Data collection and management

Data will be collected using an electronic clinical research form (eCRF) system approved by the steering committee. Each study site is responsible for data entry, and the principal investigator is responsible for confirming the final data. During the study period, a monitoring team from the contract research organization (CRO) will regularly contact and visit all sites, with occasional visits as necessary. To ensure that the study is conducted according to the protocol, the completeness, consistency, and accuracy of the data entered in the eCRF will be evaluated at each visit of the CRO. All adverse events are graded according to CTCAE v5.0 and recorded in the eCRF. The investigators are responsible for evaluating the causal relationship between protocol treatments and each event. Furthermore, they will report severe adverse events to both their institutional review board and the principal investigator. The independent Data and Safety Monitoring Board (DSMB) will monitor the recruitment, reported adverse events, and data quality when 10% (36), 30% (109), 50% (182), 70% (255), and 100% (364) of the participants are enrolled. The goal is to ensure that the study conforms to the current standards of Good Clinical Practice, with focus on the safety interests of the patients. The DSMB will provide the principal investigator with recommendations regarding potential trial modification, continuation, or premature termination.

### Current status

The study protocol was approved by the ethics committee of Kyungpook National University Chilgok Hospital on October 17, 2019 (No. KNUCH 2019-09-004-001) as well as the approval of ethics committees of all other participating institutions. Patients have been enrolled in the study since September 2021, and as of July 16, 2023, a total of 182 patients have been recruited.

## Discussion

Recent clinical studies have achieved promising results in reducing distant metastasis in LARC using TNT compared with surgery first or traditional preoperative CRT followed by surgery. Although the long-term outcomes of TNT in terms of OS and DFS are still awaited, TNT has emerged as an alternative to conventional treatment, potentially redefining the standard of care. At the time of launching the present trial, only one randomized clinical trial (POLISH II [27]) has been published. Thereafter, several randomized clinical trials using TNT have been published (RAPIDO [4], PRODIGE23 [6], STELLAR [5], FOWARC [28], CAO/ARO/AIO-12 [29], and OPRA [30]). These clinical trials differ in terms of the inclusion criteria, treatment schedules, type of radiotherapy and chemotherapy, and primary endpoints, the details of which can be found in Kang’s review article [31]. Because there are various combinations of them, a head-to-head comparison among all currently developed regimens is impossible.

This SOLAR trial compares the neoadjuvant treatment protocols (SCRT followed by four cycles of mFOLFOX6 vs. CRT) in rectal cancer with cT3–4, cN+, or extramural venous invasion. This trial is designed for mid- or low rectal cancer (tumor height  ≤ 10 cm from the anal verge) as upper rectal cancer can sometimes be treated like colon cancer and surgery can be modified as tumor-specific mesorectal excision [32]. As regards the chemotherapy duration, we adopted four cycles of mFOLFOX6 because the ypCR rate was as low as 11% with SCRT followed by three cycles of mFOLFOX6 in our initial experience [33]. Meta-analysis of 17 studies comparing SCRT followed by consolidation chemotherapy with CRT supports using at least four cycles of consolidation chemotherapy following SCRT to achieve improved ypCR and DFS over preoperative CRT alone [34]. Because SCRT followed by four cycles of CAPOX achieved significantly higher ypCR rate and 3-year OS than CRT alone in the STELLAR trial [5] involving patients with cT3–4 or cN+, the results of this SOLAR trial are awaited.

Although the RAPIDO trial used SCRT in a TNT arm, it compared a TNT regimen with longer chemotherapy duration with conventional CRT in LARC with high-risk features such as cT4, mesorectal fascia involvement, cN2, lateral lymph node metastasis, and extramural venous invasion [4]. The PRODIGE 23 trial included patients with LARC (cT3–4 or cN+) and administered induction chemotherapy with FOLFIRINOX in a TNT group [6]. The CAO/ARO/AIO-12 [29] and OPRA [30] trials compared induction and consolidation chemotherapies, and the results favored consolidation chemotherapy in the aspects of ypCR and organ preservation.

In this SOLAR trial, all patients are planned to undergo TME, without the option for nonoperative management, which is a trending approach for LARC. We plan to develop criteria for accurately diagnosing clinical complete response by leveraging the clinical and pathologic outcomes of this study, thereby informing future treatment protocols involving watchful waiting.

Our current treatment protocol presents a practical alternative, addressing concerns about potential over-treatment associated with TNT and the missed treatment opportunity of a watchful waiting strategy.

Studies comparing the cost-effectiveness of various preoperative treatment options in patients with LARC are scarce. The direct medical cost was lower in SCRT than in CRT [35]. Practically, patients should visit the hospital for 25–30 consecutive days for CRT, which influences indirect cost and QoL. This can pose a particular challenge in situations where cancer treatment is centered at designated hospitals or in countries with low health-care budgets. Two recent trials, the POLISH II [36] and ESCORT trial [9], compared the cost-effectiveness of two preoperative strategies, namely, SCRT plus chemotherapy and CRT in patients with LARC. These trials demonstrated that SCRT plus consolidation chemotherapy was more cost-effective than CRT for direct and/or indirect costs. To achieve patient-centered care, new treatments should improve not only the oncological outcomes but also the QoL for patients undergoing treatment. In this regard, the SOLAR trial will also include cost-effectiveness analysis as a secondary endpoint.

The quality of surgical resection is well known to be a crucial factor in local control and sphincter preservation following preoperative treatment and surgical resection [37]. In particular, surgical quality assessment is important in evaluating the effects of new preoperative treatments when TME is performed. Recent clinical trials have reported a wide range of complete TME, R0 resection, and sphincter preservation rates for LARC. The rates of complete TME were 81% in POLISH II and 86% in PRODIGE 23 trials; however, the rates were not reported in the RAPIDO and STELLAR. Furthermore, in POLISH II, PRODIGE 23, RAPIDO, and STELLAR trials, the R0 resection rates ranged from less than 80 to 90% and the rates of a permanent stoma during the initial TME ranged from 14 to 48%. These outcome variations may be partly attributed to differences in the inclusion criteria among the studies. Although TME with sufficient quality is currently accepted as a logical approach, the quality control of surgery may not be as standardized as that for preoperative treatment protocols. Thus, we paid particular attention to surgical quality control in our study to minimize surgical outcome variations. We are only inviting surgeons who had completed a fellowship in colorectal surgery and met the minimum criteria for experience in TME. The TME procedures of each surgeon are evaluated by the research steering committee through a review of unedited video. The details of surgical procedures such as TME and sphincter preservation will be regularly discussed in the investigator meetings to maintain consensus on surgical procedures until enrollment of the last case.

## Conclusions

The present trial is a multicenter prospective randomized controlled trial comparing SCRT followed by mFOLFOX6 and CRT as two preoperative treatments for LARC. Based on the similar effect on local control between SCRT and CRT as well as the potential systemic effect of neoadjuvant systemic chemotherapy, we hypothesized that preoperative treatment with SCRT and mFOLFOX6 would lead to longer DFS. Quality control measures are implemented to reduce surgery-related complications and achieve competent sphincter preservation, while ensuring adequate local tumor control.

## Data Availability

Data sharing is not applicable to this article as no datasets were generated or analysed during the current study.

## Abbreviations

5-FU: 5-Fluorouracil
CRT: Chemoradiotherapy
CEA: Carcinoembryonic antigen
CRO: Contract research organization
CT: Computed tomography
CTCAE: Common Terminology Criteria for Adverse Events
DFS: Disease-free survival
DSMB: Data and Safety Monitoring Board
eCRF: Electronic clinical research form
EOTRC QLQ: European Organization for Research and Treatment of Cancer Quality of Life Questionnaire
IIEF: International Index of Erectile Function
ITT: Intention-to-treat
LARC: Locally advanced rectal cancer
LARS: Low Anterior Resection Syndrome
MRI: Magnetic resonance imaging
OS: Overall survival
pCR: Pathological complete response
QoL: Quality of life
SCRT: Short-course radiotherapy
TME: Total mesorectal excision
TNT: Total neoadjuvant therapy
TRG: Tumor regression grade
